## Methods/design

### Study design and timeline

This research will use a stepped wedge cluster randomized controlled trial (SW-CRCT) design. It is commonly used to evaluate service delivery or policy interventions of clusters [26]. This research will be implemented in Beijing, whose sixteen districts are defined as the clusters. We assign the sixteen districts into four research groups using stratified randomization, with four districts in one group. The open cohort SW-CRCT will last 2.5 years, which is anticipated to be conducted from July, 2020 to December, 2022. Five continuous observational periods at a 6-month interval are divided. According to the standard design of SW-CRCT, in the first 6-month “the initial period”, no group is exposed to the additional partner notification intervention. After that, the four groups begin to cross from the control condition to receive the partner notification intervention sequentially at 6-month intervals. Once one group receives the partner notification intervention, the intervention will continue until the end of the research. And at the last 6-month period, all of the four groups will receive the additional partner notification intervention. (Fig. 1).

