### Eligibility and exclusion criteria for participants

Eligibility criteria of participants in this research include: (1) biologically male, (2) have oral or anal sex with men at least once during their lifetime, (3) aged 15 years or older, (4) have no difficulty using a mobile phone, (5) willing to provide their mobile phone numbers to serve as the unique identification numbers of the app’s self-query and partner notification functions, (6) willing to use the app’s function modules, (7) willing to complete the questionnaire for the research, (8) willing to continuously receive HIV and STDs testing and consulting services provided by the CBO our research setting at, and (9) willing to complete the informed consent document. MSM who had serious physical disabilities or mental diseases will be excluded.

MSM who meet all the eligibility criteria, but whose first HIV test results are positive, will also be invited to register as app users and complete the questionnaire. However, they will not be included in the statistical analysis of HIV incidence and other outcomes except for social network related outcomes.

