### Outcomes

The primary outcomes of this research are the HIV positive seroconversion rate (HIV incidence) and the additional cost of the intervention. The HIV positive seroconversion rate is calculated as the number of HIV positive seroconversions divided by the total number of person-years. The additional cost of the intervention is calculated as the total cost and average cost for per participant of the integrated intervention model and each additional intervention/service based on the existing HIV prevention measures provided as before.

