### Analysis

Descriptive analysis will be used to summarize the socio-demographic characteristics, HIV and STDs incidences, as well as knowledge, attitudes and related behaviors of total participants and different subgroups. To investigate the effects of the additional partner notification intervention, we will compare the differences of these primary and secondary outcomes in the control period and in the intervention period. As the HIV and STDs infection and most of the secondary outcomes are categorical variables, the generalized linear mixed models (GLMM) will be used for analysis. The model will include intervention status (in intervention period or not) and time as fixed effects and clusters (the districts) and individuals as random effects. The estimated effects of partner notification will be reported as risk ratio (RR) for binary outcomes and mean difference for continuous outcomes. 95% confidential intervals (CI) and *p* values will also be reported. The total and average additional costs of the intervention will be calculated to reflect the cost-effectiveness of the additional interventions, and the differences of these indicators in the control period and intervention period will be compared. Based on the connections recorded in the partner notification records of the database, social network visualization will be conducted to reflect the real connections of the participants. Social network analysis, such as calculation of degree, density, clique, degree centrality, closeness centrality, betweenness centrality, clustering coefficient, and so on, will be used to describe the characteristics of the social networks. Several transmission models of HIV and STDs will be formed to reflect the diseases transmission among MSM.

Sub-analysis will include: comparison of the effects in different age groups, different sex roles (insertive only, receptive only, both), different usage of HIV and STDs testing services (“Mailing rapid test reagent kit” only, the facility-based only, both). A sensitivity analysis will be conducted to evaluate the cluster (the district)-level effect. We will use the outcomes of each district across the follow-ups as the dependent variable, and fit a linear mixed model with the random effect of clusters (the districts).

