## Discussion

One important reason that HIV keeps increasing among MSM in China is that most MSM seeking causal sexual partners through online dating platforms (such as Blued and Zank), as it results in much more risk sexual behaviors for HIV and other STDs transmission [30, 31]. Partner notification of HIV and STDs infection statuses before they decide to meet and have sex can be an important and feasible method to reduce the HIV and STDs transmission among sexually active MSM. China’s Internet penetration rate has reached 61.2% by June 2019, and 99.1% of Internet users use mobile phones to surf the Internet [32]. The intervention tools based on the WeChat-the most popular mobile phone social software [33], and a website-based app enable the method more acceptable, convenient and intimate for MSM. It may lead to better effects compared with the existing partner notification methods provided by health workers individually or through email cards. An observational study using the previous version of this app has shown a potential positive effect of the app-based partner notification intervention in reducing HIV infection among MSM [29]. An encouraging finding was that the longer the app was used, the lower the HIV incidence (> 5 months vs ≤ 5 months: 2.22 per 100 person-years vs 6.99 per 100 person-years; risk ratio 0.32, 95% CI 0.12–0.87), and the app has also been proved to be user-friendly and could be accepted and widely used by MSM [29]. However, the blank control without receiving the partner notification intervention was lacking in the observational study. Meanwhile, the observation period was only 1 year and the sample size was small, so the effectiveness of the intervention needs to be further evaluated by this trial.

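### The individual random effect planned for HIV incidence is only weakly identified and cannot be told apart from a real fall in incidence with time since enrolment

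*Protocol article*

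**What the plan says.** The Analysis section of the protocol article gives a single reason and a single model: "As the HIV and STDs infection and most of the secondary outcomes are categorical variables, the generalized linear mixed models (GLMM) will be used for" (the quote breaks off one word before the sentence ends). Its terms are intervention status and "time as fixed effects and clusters (the districts) and individuals as random effects". On reporting it adds: "The estimated effects of partner notification will be reported as risk ratio (RR) for binary outcomes".

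The Outcomes section defines the primary endpoint on person-time: "The HIV positive seroconversion rate is calculated as the number of HIV positive seroconversions divided by the total number of person-years". The eligibility section takes men who are HIV-positive at their first test out of this analysis: "they will not be included in the statistical analysis of HIV incidence and other outcomes except for social network related outcomes". The design section states: "The open cohort SW-CRCT will last 2.5 years". The recruitment section lets men enter from the start until the last six months. Calendar period and time since enrolment are therefore different clocks.

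**The concern.** An individual random effect suits outcomes measured repeatedly on the same man, such as knowledge scores or sexual behaviour from the baseline and follow-up questionnaires. HIV infection is different. Each man in the incidence analysis gives a run of negative results that ends in at most one positive. Nothing is replicated within a man from which to estimate how much men differ.

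The information that remains is indirect. If men differ in risk, those at high risk convert early, and incidence among those still at risk declines with time since enrolment. A decline for any other reason looks the same to the model. Such a decline is plausible because control-period participants already receive the app, health education and testing prompts. The Discussion also reports, from an earlier observational study, that "the longer the app was used, the lower the HIV incidence". The planned fixed effects contain a term called time but none named as time since enrolment, so a real decline would be read as differences between men. At stake is whether the reported ratio estimates the ratio of incidences that the Outcomes section defines, and how wide its interval is.

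**Working it through.** **Inputs.** From Sample size: incidence 7% (control) and 5% (intervention), 16 districts, 4 steps, 30% loss, 6172 men. From the design and recruitment sections: five 6-month periods, with entry in the first four. From the Discussion: 2.22 and 6.99 per 100 person-years by duration of app use.

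**The plan's own figures.** 5/7 = 0.714. 16 × 270 = 4320, and 4320/0.70 = 6171.4, rounded up to 6172. 2.22/6.99 = 0.32. All reproduce.

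**Why the variance is weakly identified.** Let man i have hazard u_i·h0(t), with t the time since enrolment and H0 the cumulative h0. One event per man reveals only the marginal hazard h0(t)·E[u | still at risk at t]. With gamma-distributed u of variance θ this is h0(t)/(1 + θ·H0(t)). A declining marginal hazard can thus come from a declining h0 with θ = 0, or from a constant h0 with θ > 0. Only the assumed distribution and form of h0 choose between them.

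**Simulation.** Assumptions: 7% is read as annual, so 3.5% per half-year; even entry over periods 1 to 4; 8.5% dropout per half-year (1 − 0.915^4 = 0.30); no district effect; follow-up ends at seroconversion; no true differences between men; true ratio 0.714. Each data set was fitted with period effects, with and without a normal individual intercept. A fall means that incidence drops to the stated fraction after the first half-year in the cohort. There were 80 to 300 runs per scenario.

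| Fall | Fit | Individual SD (estimated) | Ratio with / without the term | SE of log ratio with / without |
|---|---|---|---|---|
| none | cloglog | about 0 in 53% of runs | 0.712 / 0.713 | – / 0.116 |
| none | logit | about 0 in 54% | 0.692 / 0.700 | 0.120 / 0.118 |
| none | person-time Poisson | about 0 in 56% | 0.702 / 0.704 | 0.117 / 0.116 |
| to 0.6 | cloglog | 2.16 | 0.685 / 0.722 | 0.160 / 0.133 |
| to 0.6 | logit | 2.38 | 0.683 / 0.728 | 0.174 / 0.135 |
| to 0.6 | person-time Poisson | 1.47 | 0.718 / 0.731 | 0.143 / 0.133 |
| to 0.32 | cloglog | 4.02 | 0.622 / 0.716 | 0.235 / 0.152 |
| to 0.32 | logit (odds ratio) | 4.81 | 0.591 / 0.709 | 0.276 / 0.154 |
| to 0.32 | person-time Poisson | 2.03 | 0.689 / 0.711 | 0.175 / 0.153 |

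The comparison to read is within a row. The logit and person-time rows rest on 80 runs, so the log ratio carries simulation error of about 0.144/√80 = 0.016. Rescaled to a true 0.714, the person-time row for a fall to 0.6 gives 0.714 × 0.718/0.731 = 0.70. Separate large-sample cloglog fits gave 0.706 (SD 2.1) for a fall to 0.6, 0.68 (SD 4.1) for a fall to 0.32, and no change when incidence is flat. A Poisson fit per interval put the SD at 0 in every run, so there the term did nothing.

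For cloglog and a fall to 0.32, the SE is 0.235/0.152 = 1.55 times as large, coverage of the 95% interval is 88% against 93%, and power is 52% against 60%.

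**No true effect, fall to 0.32 (cloglog).** Ratio 1.008 with the term; type I error 7% against 6%; SE 0.215 against 0.140.

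**Men truly differ (normal SD 2), no other fall (cloglog).** Estimated SD 1.94; ratio 0.715 with the term, 0.744 without. With a true SD of 1, the estimate was still 0 in 17% of runs.

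**Time since enrolment.** With even recruitment, adding it to the model without the individual term leaves the ratio as it was. If recruitment in opened districts ran at 0.5, 1.5 or 2 times the usual speed, with a fall to 0.6 and a true ratio of 1, calendar time alone gives 0.95, 1.04 and 1.07 (0.87, 1.10 and 1.19 for a fall to 0.32). With time since enrolment the ratio is 1.00 in every case, and the SE changes by no more than 0.001.

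**The case against.** A reader might infer that the term cannot be estimated at all, or that it exaggerates the primary ratio as a rule. The documents and the calculations support neither. Under the parametric model a true SD of 2 was recovered. With flat incidence nothing changes, with a true ratio of 1 only the width suffers, and under one common layout the term vanishes. Men may well differ: the Background quotes 8.5 against 2.0 per 100 person-years for dating-app users and nonusers. In that case the term moves the estimate towards the conditional ratio.

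It is also tempting to take the Discussion's 6.99 against 2.22 as the fall to expect in this trial. It is not evidence of that. The contrast is by duration of use of an earlier version of the partner-notification app, in a small one-year study without a control, with an interval from 0.12 to 0.87. Nothing shows incidence falling with time since enrolment under control conditions. The 0.32 rows are an extreme case.

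The recruitment-speed figures rest on an assumption that the protocol does not document. Opening of the function is automatic, and staff are not told the scheme at the start. Nor may the once-only argument be carried straight to syphilis and hepatitis, because the article does not say whether repeat events count.

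Two further points have some force. An unseen SAP may settle the link, the row layout and the meaning of time. The planned district-level sensitivity analysis has no individual term. But that analysis is a linear model and does not replace the primary estimate, and an SAP would have to reverse a term that the article already applies to HIV infection.

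**Conclusion.** The point stands in a limited form. The individual random effect is stated for the primary outcome, where its variance is weakly identified and confounded with any real fall in incidence by time since enrolment. Harm is conditional on such a fall. For a true ratio of 0.714, the estimate moves to about 0.68 to 0.71 for a fall to 0.6 and to about 0.59 to 0.69 for a fall to 0.32. The simulated SE rises by about 20% (0.160/0.133) and 55% respectively under cloglog. There is no shift at a true ratio of 1, and none if incidence is flat.

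These sizes rest on an annual reading of 7%, even entry, no district effect and no true differences between men, and they vary with link and layout. Because HIV data with one event per man can hardly show which explanation of a fall is right, the primary ratio would rest on an assumption that the trial can barely test. This is worth correcting before analysis; it does not invalidate the design.

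**What to change.** For HIV incidence, and for syphilis, hepatitis B and hepatitis C where only the first seroconversion counts:

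- end each man's follow-up at first seroconversion;
- use a person-time or discrete-time model with district random effects and no individual random effect;
- add time since enrolment (for example 0–6, 6–12 and over 12 months) as a fixed effect beside calendar period;
- state for each of the other infections whether repeat events count.

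Keep the individual random effect for the repeated questionnaire outcomes.

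The cost is wording. The Trial status section says that recruitment and analysis had not begun, and registration through the app should supply enrolment dates. In the fits without the individual effect, the enrolment term cost practically no precision. Adding it while keeping the individual effect is a partial remedy: with a fall to 0.32 this gave 0.716 (person-time) and 0.692 (logit), but the SD was practically zero in 50% and 35% of runs.

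There is a small downside. If risk differs strongly between men, the estimate is the population incidence ratio, slightly nearer 1 than the conditional ratio: about 0.73 to 0.74 instead of 0.714 at an SD of 2, and up to 0.76 in the smaller logit and person-time runs. That population ratio is the one that matches the Outcomes section, where the rate is "the number of HIV positive seroconversions divided by the total number of person-years".

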### Study setting and recruitment

We will conduct our research in Beijing, the capital city of China with high population mobility and demographic heterogeneity and high burden of HIV and related STDs among MSM. We will cooperate with a local community-based organization (CBO) named *Man Wellness Center* to recruit participants and provide HIV and other STDs (syphilis, hepatitis B, and hepatitis C) testing services. *Man Wellness Center* is one of the largest and most popular CBO for MSM to give them HIV and STDs prevention and medical services.

Participants will be recruited in two ways: offline and online. The offline recruitment will be implemented in offline venues, such as the clinic sites of the CBO for routine work, and the gay bars, bathrooms, parks for outreach services. The online recruitment will be implemented through online platforms, such as WeChat, QQ, Weibo and Blued. The process of recruitment includes four steps: (1) Determine whether the participant recruited meets the eligibility criteria. (2) Introduce the research and tools for interventions (the app and the WeChat official account) if eligible. (3) Help the participant sign the electronic informed consent through the app and then show him the functions of the app and WeChat official account. The content of the electronic informed consent contains all necessary information as traditional paper version of informed consent, and the signed electronic informed consent will be stored in the database. Participants under the age of 18 are asked to register the app system and sign the consent accompanied by a guardian, and written consent is also obtained from the guardian. (4) Invite the participant to fill in the baseline questionnaire through the app. (5) Provide HIV and other STDs testing services and upload the test results through the backend database. The recruitment will start from the beginning of the research, and we will stop recruitment in the last 6 months of the research. If the participant has HIV and other STDs testing during the follow-up period, he will be invited to finish a follow-up questionnaire.

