### Randomization and allocation

The randomization is conducted in cluster (district) level, instead of individual level. The previous records of the CBO show that most MSM receiving HIV testing services are from the following four districts: Chaoyang, Shunyi, Fengtai, and Haidian. Considering the number balance of participants in each groups, stratified randomization is used. The process of randomization is conducted by a researcher using SAS software: (1) Assign each district a number, A1 to A4 for the four districts that the research may recruit more potential participants (Chaoyang, Shunyi, Fengtai and Haidian), B1 to B12 for other twelve districts. (2) Extract without putting it back one number in districts A and three numbers in districts B to be one sampling group. Finally, the sixteen districts will be randomized into four intervention groups. (3) Randomize the order of four intervention groups to be Group 1 to 4, and the additional partner notification intervention using app will be implemented to these groups in sequence every 6-month intervals. The participants will be assigned to different groups according to the district where they live recorded in the baseline questionnaire.

As the partner notification is a kind of behavioral intervention, it is impossible that participants do not know what intervention they receive. So, the research is only single-blind to outcome assessors. However, we take efforts to reduce the information bias caused by the non-blind design of other stakeholders. At the beginning of the research, participants, staff of the CBO, and the researchers who participate in management of participants will not know the randomized scheme of the research. The additional partner notification will be opened to participants sequentially by the predetermined computer program, which does not need CBO staffs and researchers to implement the intervention manually. The CBO staffs and researchers do not know the implementation of partner notification unless the participants tell them whether they can use the partner notification function of the app on their own initiative. Even the CBO staff knows that, the operation and results of the HIV and STDs testing will not be affected. Also, the outcomes assessors do not know the randomized scheme in the process of data analysis.

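### The primary GLMM has no district-by-period random effect, so its interval and p value overstate certainty if within-district correlation weakens between periods

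*Protocol article*

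**What the plan says.** All references are to the protocol article.

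- **Primary model (Analysis).** "The model will include intervention status (in intervention period or not) and time as fixed effects", with "clusters (the districts) and individuals as random effects". No effect for a district in a given period is named.
- **Sensitivity model (Analysis).** A linear mixed model takes each district's outcomes across follow-up as the dependent variable, with a district random effect.
- **Design (Study design and timeline).** "The open cohort SW-CRCT will last 2.5 years", split into five 6-month periods. Sixteen districts cross over in four groups of four.
- **Randomisation (Randomization and allocation).** "Considering the number balance of participants in each groups, stratified randomization is used". The reason given is that "most MSM receiving HIV testing services are from the following four districts". Each group receives one of those four districts and three of the other twelve.
- **Sample size.** Control incidence 7%, intervention 5%, alpha 0.05, power 0.90, ICC 0.01, 16 clusters, 4 steps; 270 per cluster, 4320 in total, 6172 after 30% loss. One ICC is given and no between-period correlation.

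**The concern.** A single district intercept forces the within-period and between-period correlations to be equal (ratio 1, often called a cluster autocorrelation of 1). HIV incidence in a district is likely to vary over 2.5 years because infections are passed on locally. The protocol itself plans to map transmission networks among participants (Outcomes; Analysis). Variation shared by the men of one district in one period cannot be absorbed by the individual random effect, and a binomial or Poisson likelihood has no free residual variance to take it up.

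In a stepped wedge the effect is estimated mainly by comparing periods within districts. District-by-period variation therefore feeds directly into the estimate, and a model without that term leaves it out of the standard error. At stake are the confidence interval and p value for the primary HIV incidence comparison.

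This is a stated model structure, not a detail left open. An analysis plan that follows the article would inherit it.

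**Working it through.** **1. Reproduce the plan's sample size.** The standard stepped-wedge variance for cluster-period means is

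Var = I·s²(s² + T·t²) / [(I·U − W)s² + (U² + I·T·U − T·W − I·V)t²].

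Inputs:
- I = 16 and T = 5.
- U = 40 treated district-periods.
- W = 4² + 8² + 12² + 16² = 480.
- V = 4(4² + 3² + 2² + 1²) = 120.
- Total variance 0.07 × 0.93 = 0.0651.
- t² = 0.01 × 0.0651 = 0.000651.
- s² = 0.99 × 0.0651 / 270 = 0.0002387.

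Numerator: 16 × 0.0002387 × (0.0002387 + 5 × 0.000651) = 1.334 × 10⁻⁵. Denominator: 160 × 0.0002387 + 480 × 0.000651 = 0.35067. Var = 3.805 × 10⁻⁵, so SE = 0.00617. Power = Φ(0.02/0.00617 − 1.96) = 0.900.

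So 270 reproduces as a number per district **per period**; 16 × 270 = 4320, and 4320/0.70 gives 6172. The calculation has the same ratio of 1 built in as the analysis model.

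**2. Let the correlation weaken between periods.** Keep the within-period ICC at 0.01 and let the between-period ICC be c × 0.01. The ratio c is not in the protocol; 0.5 to 1 is an assumed range. The true covariance V adds a district-by-period variance of 0.01(1 − c) × 0.0651 to each district-period mean. The working covariance M follows the stated model. With X the design matrix (period effects and intervention) and B = (X′M⁻¹X)⁻¹, the reported variance is the intervention element of B and the true variance is that of B X′M⁻¹VM⁻¹X B. With r = true SE / reported SE, actual type I error is 2Φ(−1.96/r). Equal districts, 270 per period:

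| Ratio c | Reported SE | True SE | r | Type I error |
|---|---|---|---|---|
| 1 | 0.00617 | 0.00617 | 1.00 | 5.0% |
| 0.95 | 0.00616 | 0.00655 | 1.06 | 6.5% |
| 0.9 | 0.00616 | 0.00691 | 1.12 | 8.1% |
| 0.8 | 0.00615 | 0.00757 | 1.23 | 11.1% |
| 0.5 | 0.00610 | 0.00918 | 1.50 | 19.3% |

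The reported SE hardly moves while the true SE rises by up to half.

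**3. Smaller and unequal districts.**
- If the 270 were spread over the five periods (270/5 = 54 each), sampling noise dominates and type I error is about 5% to 8% over the same range.
- If the four large districts held 750 men per period and the others 110 (assumed; mean (4 × 750 + 12 × 110)/16 = 270), it would be 8.2%, 11.4%, 17.2% and 30.2% at c = 0.95, 0.9, 0.8 and 0.5.

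**4. Check on the binomial scale.** A simulated logistic model with a district intercept and period effects (equal districts, 270 per period, 400 runs each) gave 95% interval coverage of 94.8% at c = 1, 83.2% at 0.8 and 80.2% at 0.5. Neither this nor step 2 includes an individual random effect; each treats the men in different periods as distinct.

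**5. Power once the term is included.** Replace s² by s² plus the district-by-period variance, and t² by c × 0.000651. At c = 0.8: s² = 0.0002387 + 0.0001302 = 0.0003689 and t² = 0.0005208, so Var = 1.755 × 10⁻⁵ / 0.30901 = 5.68 × 10⁻⁵, SE = 0.00754 and power = Φ(0.02/0.00754 − 1.96) = 76%. The same steps give 86% at 0.95, 83% at 0.9 and 61% at 0.5.

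**The case against.** **The district-level model already handles it.** This is the strongest reply. In a linear mixed model on district-period summaries, the residual acts as the district-by-period term. Simulation of that model (equal districts, period and intervention fixed effects assumed, normal reference) gave type I error of 4.7% to 6.6% at 270 per period and 5.7% to 6.4% at 54, for ratios from 1 to 0.5. This stands as a partial safeguard. But the model is a sensitivity analysis, so the primary interval and p value stay exposed, and the protocol does not say what happens if the two disagree.

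**The ratio might be 1.** Then the intervals are right. The protocol neither gives nor excludes any value, so the inflation is conditional.

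**Stronger readings a reader might infer, which the document does not support:**

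- *Leaving out the randomisation stratum or baseline covariates also narrows the interval.* Adding the stratum leaves the SE at 0.00617, and simulated coverage at a ratio of 0.8 is 83.2% without it and 83.5% with it. The district effect already absorbs such differences. A covariate list is ordinary analysis-plan content.
- *Recruitment after crossover biases the effect.* Enrolment does run past crossover for most groups ("we will stop recruitment in the last 6 months of the research"). But the step in which staff "show him the functions of the app and WeChat official account" follows consent and is the same in both conditions, as is the requirement to be willing to use the app. Partner notification is opened by a preset program, and staff are not told whether it is open. A change in case mix is possible but not shown.
- *The test is a liberal normal-based one.* No reference distribution is stated. Using z instead of t with 10 to 14 degrees of freedom would give 7.0% to 7.8%, but with about 59 within-district degrees of freedom it gives 5.5%. This bears on the repair and is not an error in the text.

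**Conclusion.** The point holds in a narrow, conditional form. The stated primary model assumes a district correlation that stays constant over 2.5 years, which is unlikely for a transmissible infection. If the between-period correlation is below the within-period one, the primary analysis claims more certainty than it has. With ICC 0.01, equal districts and 270 per district-period, the actual error rate of the nominal 5% test is about 6.5% to 19% for assumed ratios of 0.95 to 0.5. It is about 5% to 8% at 54 per period, and there is no inflation at a ratio of 1. Concentration of men in four districts would make it worse.

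The cause is the missing district-by-period term alone. It should be corrected before analysis, but it does not show that the trial's result would be wrong.

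**What to change.** - **Primary model.** Add a district-by-period random effect to the GLMM, or let the between-period correlation decay with time.
- **Inference.** Name a small-sample method suited to 16 unequal districts. A permutation test over the stratified randomisation scheme is one option. A fixed rule such as t with 12 degrees of freedom needs care: on the district-level model it was conservative (2.9% to 4.0%).
- **Power.** Report power over a stated range of the ratio. With the term included, 90% power needs 312, 369 or 580 men per district-period at ratios of 0.95, 0.9 and 0.8, and cannot be reached at 0.5.
- **Optional.** A sensitivity analysis of men enrolled before their district's crossover.

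The model change is wording in the analysis plan and needs no new data. The cost is a somewhat wider interval and lower power: about 83% rather than 90% at a ratio of 0.9, and 76% at 0.8. If the ratio is close to 1, little is lost.

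### HIV and STD incidence is defined per person-year, but the stated model treats infection as binary and names no person-time, so it does not estimate the declared rate

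*Protocol article*

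**What the plan says.** All references are to the protocol article.

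- **Outcomes.** The primary outcome is a rate: "The HIV positive seroconversion rate is calculated as the number of HIV positive seroconversions divided by the total number of person-years". Syphilis, hepatitis B and hepatitis C incidence, the first secondary outcome, are defined the same way.
- **Analysis, choice of model.** "As the HIV and STDs infection and most of the secondary outcomes are categorical variables, the generalized linear mixed models (GLMM) will be used".
- **Analysis, model terms.** "The model will include intervention status (in intervention period or not) and time as fixed effects and clusters (the districts) and individuals as random effects".
- **Analysis, effect measure.** "The estimated effects of partner notification will be reported as risk ratio (RR) for binary outcomes". The only other measure named is a mean difference for continuous outcomes. No offset, count model, survival model or rate ratio is mentioned.
- **Study design and timeline.** "The open cohort SW-CRCT will last 2.5 years" and "Five continuous observational periods at a 6-month interval are divided".
- **Study setting and recruitment.** Recruitment runs from the start and stops for the last 6 months. Follow-up data arise when a participant has a test.

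**The concern.** A rate and a risk agree as effect measures only if time at risk is comparable between the conditions. Here it varies from man to man. Men enter over two years, retest when they choose to, and 30% are expected to be lost. A seroconversion is seen only if the man tests again. If infection is analysed as yes or no without person-time, any difference in observed time between control and intervention passes directly into the risk ratio.

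Such a difference is plausible, because the Discussion expects the intervention to improve testing adherence, which is itself a secondary outcome. What is at stake is the primary effectiveness estimate and three secondary incidence outcomes.

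**Working it through.** **1. The sample size as corroboration.** The Sample size section gives 16 clusters, 4 steps of 4 clusters, 7% vs 5%, α 0.05 (two-sided, per Analysis), ICC 0.01 and power 0.90. The Hussey-Hughes variance is

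Var = Iσ²(σ² + Tτ²) / [(IU − W)σ² + (U² + ITU − TW − IV)τ²]

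- I = 16, T = 5, U = 40, W = 480, V = 120, so IU − W = 160 and U² + ITU − TW − IV = 480.
- Total variance 0.07 × 0.93 = 0.0651; τ² = 0.01 × 0.0651 = 0.000651; σ² = 0.99 × 0.0651 / 270 = 0.0002387.
- Var = 16 × 0.0002387 × 0.003494 / (0.03819 + 0.31248) = 0.00003805, so SE = 0.00617.
- Power = Φ(0.02/0.00617 − 1.96) = Φ(1.28) = 0.900.

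So 270 is reproduced as the number per cluster and 6-month period. Then 16 × 270 = 4320, and 4320/0.70 = 6171.4, rounded up to 6172. The planning calculation is thus a comparison of proportions per period, with no person-time. This fits the binary reading of the Analysis section.

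**2. Observed time when only calendar time matters.** Assume equal districts, each recruiting one unit of men in each of periods 1 to 4, with uniform entry within a period and no loss. A new man is observed for 0.25 years in his entry period, and an existing man for 0.5 years.

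| Period | Mean years per man-period, any district |
|---|---|
| 1 | 0.250 |
| 2 | 0.375 |
| 3 | 0.417 |
| 4 | 0.4375 |
| 5 | 0.500 |

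Within a period these means do not depend on condition. Under no effect:

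- Man-period rows with period effects: ratio 1.000.
- Man-period rows without period effects: control 7.5 years over 20 man-periods = 0.375; intervention 16.5 over 36 = 0.458; ratio 0.458/0.375 = 1.22.
- One row per man per condition: control 7.5 years over 10 men = 0.75; intervention 16.5 over 16 = 1.03; ratio 1.03/0.75 = 1.37. It is 1.31 with front-loaded recruitment and 1.41 with 10% loss per period.

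**3. Observed time that differs by condition within a period.** The unit is the man-period, period and district effects are fitted, and there is no true effect.

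- Observed time multiplied by 0.9 or 1.1 under intervention: ratio 0.90 or 1.10.
- Recruitment doubled under intervention. In period 2 the first group then has one existing and two new units, (0.5 + 2 × 0.25)/3 = 0.333 years against 0.375 in control, a ratio of 0.89. Fitted over all periods the ratio is 0.92. With recruitment multiplied by 1.25 it is 0.97.

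**4. With a person-year offset.** With period and district effects, the ratio under no effect lies between 0.996 and 1.003 in every scenario tried. With a true ratio of 5/7 = 0.714 and recruitment multiplied by 1.25 to 2, the offset model gives 0.718. The model without person-time gives 0.699 to 0.659.

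The fits in steps 3 and 4 used expected counts at 0.07 per person-year in control, with fixed district-group effects in place of the random effects.

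**The case against.** **A mixed model can carry an offset.** The GLMM family includes Poisson models with person-time, and link and offset are commonly left to a statistical analysis plan that is not shown here. This would answer the point if the article were silent. It is not: it gives a reason for the model (infection is categorical), its terms and its effect measure, and these do not match its own outcome definition.

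**The label proves little.** The Discussion calls 2.22 vs 6.99 per 100 person-years a risk ratio of 0.32. A reader might take the words risk ratio in the Analysis section as proof that person-time is ignored. They are not. The point rests on the stated rationale and on the absence of person-time from the listed terms.

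**Time is in the model.** A reader might infer that the open cohort by itself makes unequal observation time look like an intervention effect. The article does not support that: with man-period rows, entry and loss patterns common to all districts cancel (step 2). One row per man per condition, which gives the largest figures, sits awkwardly with a time effect over five periods, although the unit is not stated.

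**The design limits differential observation.** Test prompts, education and self-query run in both conditions. The scheme is concealed at the start, and the function opens by computer program. This stands as a reason to expect modest differences. It does not remove the effect on testing that the Discussion itself expects.

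**Large distortions are hard to reach.** A reader might suppose that the planned effect could be erased. With man-period rows that needs observed time 40% higher under intervention, hence a control mean of at most 6/1.4 = 4.3 months of a possible 6. With a control mean of 5.25 months the largest possible rise is 6/5.25, or 14%.

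**Conclusion.** The mismatch holds. The declared primary outcome and three secondary outcomes are person-year rates, and the analysis as stated is a binary one that does not estimate them.

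Bias in the intervention effect is possible but not established. It requires observed time to differ by condition within a period (through testing, retention or recruitment), or a unit of one row per man per condition. Its direction is open: fuller observation under intervention pushes the ratio up, and more new entrants push it down. The illustrative ratios under no effect, 0.92 to 0.97, 1.10, and 1.31 to 1.41, rest on assumed recruitment and follow-up patterns that the article does not give.

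The individual random effect should not be read as an error. Each man contributes at most one seroconversion, so that variance may be weakly identified for HIV. However, the article gives one generic model for all outcomes, including repeated questionnaire measures, and no calculation shows that the term distorts the HIV estimate.

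**What to change.** For HIV, syphilis, hepatitis B and hepatitis C incidence, the Analysis section should:

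- state the unit as man by 6-month period;
- fit a Poisson (or complementary log-log) mixed model with log person-time at risk as offset, categorical period effects, intervention status and a district random effect;
- split person-time at the district's crossover and end it at seroconversion or last test;
- report an incidence rate ratio with its 95% confidence interval.

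Whether to keep the individual random effect for these outcomes is a secondary choice.

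The cost is revised wording and slightly more data preparation. Test dates are already held according to Data management, so no new data are needed. Trial status says that recruitment and analysis had not begun at the time of writing, so the change could be specified in advance.
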